### 2.5. Statistical Procedures

#### 2.5.1. Sample Size

The sample size calculation was performed following the indications by Donner et al. [43]. First, we calculated the sample sizes without adjustment for clustering (*N_0_*). For this purpose, the statistical analysis in this study involved several parameters, including the threshold probability for rejecting the null hypothesis (α), which represents the type I error rate, and the probability of failing to reject the null hypothesis under the alternative hypothesis (*β*), representing the type II error rate. In addition, the proportion of subjects in the intervention group (*q*_1_) and control group (*q*_0_), the effect size (Cohen’s *d*), and the standard deviation of the outcome in the population (*σ*) were calculated. Thus, an *α* value (two-tailed) of 0.05 and a *β* value of 0.20 were established so that the standard normal deviation for *α* is *Z_α_* = 1.960 and for *β* is *Z_β_* = 0.842. The proportion of subjects in both the intervention and control groups will be similar (*q*_1_ = 0.50; *q*_0_ = 0.50). Our study will be powered to detect medium-sized effects (i.e., Cohen’s *d* = 0.5), and the standard deviation of the outcome in the population will be 1.0.
$$N_{0}=\frac{\left(\frac{1}{q_{1}}+\frac{1}{q_{0}}\right)\;*\;(\left(Z_{\alpha \;}+Z_{\beta }{)}^{2}\right)}{{\left(\frac{d}{\sigma }\right)}^{2}}$$
$$N_{0}=\frac{\left(\frac{1}{0.50}+\frac{1}{0.50}\right)*(\left(1.960+0.842{)}^{2}\right)}{{\left(\frac{0.5}{1.0}\right)}^{2}}$$
*N*_0_ = 125.58 ≈ 126 participants

Second, we calculated the sample size with adjustment for clustering (*N*_1_). For previous studies in this specific population, we assumed an average household size (*m*) of 1.2 participants according to previous studies performed in the same region [44,45]. Moreover, the within-cluster correlation coefficient (*ρ*) was established as 0.5.
Design effect = 1 + (*ρ* × (*m* − 1))
Design effect = 1 + (0.5 × (1.2 − 1)) = 1.1
*N*_1_ = *N*_0_ × Design effect => 138.14 ∗ 1.1 = 138.142 ≈ 138 participants

Third, we further assumed a 10% drop-out rate, which was estimated using the following formula:*N*_3_ = *N*_2_ / (1 − % losses)
*N*_3_ = 138/(1 − 0.1) = 153 participants

Thus, a minimum sample size of 153 participants for the whole sample will be required to perform this study.

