## Abstract

**Objective:** The aim of this paper is to describe the protocol of pilot cluster randomized controlled trial (RCT) that will evaluate the effects of a lifestyle-based intervention. The *Archena Infancia Saludable* project will have several objectives. The primary objective of this project is to determine the 6-month effects of a lifestyle-based intervention on adherence to 24-h movement behaviors and Mediterranean diet (MedDiet) in schoolchildren. The secondary objective of this project is to test the intervention effects of this lifestyle-based intervention on a relevant set of health-related outcomes (i.e., anthropometric measurements, blood pressure, perceived physical fitness, sleep habits, and academic performance). The tertiary objective is to investigate this intervention’s “halo” effect on parents’/guardians’ 24-h movement behaviors and adherence to the MedDiet. **Methods:** The *Archena Infancia Saludable* trial will be a cluster RCT submitted to the Clinical Trials Registry. The protocol will be developed according to SPIRIT guidelines for RCTs and CONSORT statement extension for cluster RCTs. A total of 153 eligible parents/guardians with schoolchildren aged 6–13 years will be randomized into an intervention group or a control group. This project focuses on two fundamental pillars: 24-h movement behaviors and MedDiet. It will mainly focus on the relationship between parents/guardians and their children. Behavior change strategies for dietary and 24-h movement behaviors in schoolchildren will be based on healthy lifestyle education for parents/guardians through infographics, video recipes, brief video clips, and videos. **Conclusions:** Most of the current knowledge on 24-h movement behaviors and adherence to the MedDiet is based on cross-sectional or longitudinal cohort studies, warranting a need to design and conduct RCTs to obtain more robust evidence on the effect of a healthy lifestyle program to increase 24-h movement behaviors and to improve adherence to the MedDiet in schoolchildren.

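### The target of 153 is given as cluster members in section 2.5.1 but as randomised parents/guardians in the abstract; its design effect is also slightly too small and it is rounded down

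*Protocol article*

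**What the plan says.** Section 2.5.1 (Sample Size) works in three steps. It finds an unclustered total of 125.58, or 126. It multiplies by a design effect of 1 + 0.5 × (1.2 − 1) = 1.1 to reach 138. It then divides by 0.9 for 10% drop-out and reports 153. The cluster is a household, with an average size "of 1.2 participants according to previous studies performed in the same region". The conclusion is: "Thus, a minimum sample size of 153 participants for the whole sample will be required to perform this study".

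The abstract gives the same number as "A total of 153 eligible parents/guardians with schoolchildren", who are to be randomised. Section 2.2.1 (Procedure) makes the participating parents/guardians the unit of randomisation and of cluster analysis. Section 2.6.1 measures the primary outcomes in schoolchildren. Section 2.5.2 evaluates the intervention effect with multilevel mixed-effects models.

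**The concern.** An individual-level sample size multiplied by a design effect is a count of cluster members. The abstract uses the same count for the clusters. The two agree only if every household contributes one child, and then no design effect would be needed. A reader of the abstract would expect about 20% more children than a reader of section 2.5.1, and the two readings imply different power.

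Two further features make 153 a little too small on the section 2.5.1 reading. No set of equal-sized households averages 1.2, so the equal-cluster formula evaluated at the mean understates the inflation. And a number described as a minimum has been rounded down.

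**Working it through.** **Inputs, all from section 2.5.1.** Two-sided α = 0.05 and β = 0.20 (z values 1.960 and 0.842); d = 0.5 ("Our study will be powered to detect medium-sized effects"); "the standard deviation of the outcome in the population will be 1.0"; equal allocation; mean household size m = 1.2; within-household correlation ρ = 0.5; loss 10%.

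**Reproducing the plan's figure.**
- N0 = (1/0.5 + 1/0.5) × (1.960 + 0.842)² / 0.5² = 125.6. The plan's 125.58 comes from unrounded z values.
- N1 = 125.58 × 1.1 = 138.14, cut to 138.
- 138 / 0.9 = 153.33, cut to 153.

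So 153 reproduces apart from the rounding. The printed product is wrong as typed: it multiplies 138.14 by 1.1, which would be 151.95. The multiplicand should be 125.58, and the printed result is right. The drop-out formula also starts from an N2 that is never defined; N1 is evidently meant.

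**Unit.** A household with a participating parent and a participating child has at least two members, so 1.2 cannot count both. On the primary outcome the members are children.
- 153 children: 153 / 1.2 = 127.5, or about 128 households.
- 153 parents/guardians, assuming one per household: 153 × 1.2 = 183.6, or about 184 children.

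**Rounding.** 153 × 0.9 = 137.7, just under the 138.14 required. Rounding up only at the end gives 154 (from 153.33). Rounding up at both steps gives 139 / 0.9 = 154.4, so 155. The loss of power is about 0.1 point (79.9% at a design effect of 1.1).

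**Design effect with unequal households.** For an efficiently weighted mixed model it is E[m] / E[m / (1 + (m − 1)ρ)]. The article gives only the mean, so the size mix is an assumption.
- 80% with one child and 20% with two, the least variable mix with mean 1.2: 1.2 / (0.8 × 1 + 0.2 × 2/1.5) = 1.2 / 1.0667 = 1.125.
- 90% with one child and 10% with three, the most variable mix tried: 1.2 / (0.9 × 1 + 0.1 × 3/2) = 1.2 / 1.05 = 1.143.

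The 80/20 mix gives the smallest possible value, so 1.1 is too small whatever the true mix.

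**Power.** Φ(0.25 × √(completers / design effect) − 1.96), with no credit for baseline:

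| Reading | Completers | Design effect | Power |
|---|---|---|---|
| 153 children | 137.7 | 1.1 (as planned) | 79.9% |
| 153 children | 137.7 | 1.125 | 79.0% |
| 153 children | 137.7 | 1.143 | 78.4% |
| 153 parents | 165.2 | 1.1 (as planned) | 86.5% |
| 153 parents | 165.2 | 1.125 | 85.8% |

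**Children needed for 80% at 1.125.** 125.58 × 1.125 / 0.9 = 156.98, so 157. Rounding up at each step, 126 × 1.125 = 141.75, so 142, and 142 / 0.9 = 157.8, so 158. Over the mixes tried the requirement runs from 157 to 160.

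**The case against.** The best defence is that little power is at stake. The trial is a pilot in one school, 153 is a minimum rather than a stopping number, and section 2.2.4 invites every eligible family. The rounding costs about 0.1 point, and the design effect about 1 point under the planned model. The calculation also takes no credit for the baseline measurement. If the model adjusts for baseline with variance factor 1 − r², an assumed correlation of 0.2 would lift 79.0% to 80.6%, and 0.3 would lift it to 82.6%. The article gives no such correlation, so this is only illustrative.

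All of that stands, and it limits the size of the point. It does not answer the conflict of units, which is in the printed text and does not depend on any assumed household mix.

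Three stronger readings are tempting, and the document does not support them.
- A reader might infer that the trial misses 80% power whatever 153 means. On the abstract's reading, power is above 80%.
- A reader might take the whole sample to mean parents plus children, which would leave far fewer children. The phrase closes a calculation built on the shares of the two arms, so it naturally means both arms together, and a household size of 1.2 cannot count both generations.
- A reader might apply the larger design effect for an unweighted comparison, 1 + 0.5 × (1.6/1.2 − 1) = 1.167, which gives 77.5% for 153 children. Section 2.5.2 lists simple two-group tests but evaluates the intervention effect with mixed models, so 1.125 is the relevant figure.

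**Conclusion.** The point holds, mainly as a contradiction in what 153 counts: children in about 128 households by the algebra of section 2.5.1, or randomised parents/guardians with about 184 children by the abstract. The second reading has 20% more children than the first.

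The design effect of 1.1 is too small for any household mix averaging 1.2, and the final figure is rounded down, but together they cost only about 1 to 1.6 points. For 153 children, power under the planned mixed model is 78.4% to 79.0%, slightly below the stated 80%. For 153 parents it is about 86%.

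These figures rest on the plan's own d, ρ and loss rate, on household mixes with up to three children, on one participating parent per household, on loss that leaves the household mix unchanged, and on no gain from baseline. The document does not support a general claim that the trial is underpowered.

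**What to change.** State the target in one unit, in the same words, in the abstract and in section 2.5.1, with the power that belongs to it:
- if children are meant: 153 children from about 128 households, power about 79% allowing for unequal household size; or
- if households are meant: 153 parents/guardians, one per household, with about 184 children, power about 86%.

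If the full 80% is wanted on the children reading, set the target at 157 to 158 children (158 / 1.2 = 131.7, about 132 households), using the design effect of 1.125, stating the assumed mix and rounding up.

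Correct the printed product to 125.58 × 1.1 = 138.14, and replace the undefined N2 in the drop-out formula with N1.

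The cost is a restated figure and a few words. Keeping 153 children with restated power needs no extra recruitment, and restoring 80% needs four or five more children. If households are meant, no recruitment is added beyond what the abstract already states.

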#### 2.5.2. Statistical Analysis

The mean (*M*) and standard deviation (*SD*) will be provided for quantitative variables, while frequencies (*n*) and percentages (%) will be given for qualitative variables. Kolmogorov-Smirnov’s test with Lilliefors correction and Levene’s test will be used to assess the normality of data and the equality of variances, respectively. Thereafter, Student’s *t* test or Mann–Whitney’s *U* test for two-group comparisons will be used in relation to meeting the normality assumption. Pearson’s chi-square (χ^2^) test will be employed to verify associations between qualitative variables. For quantitative variables, the relationship will be tested through Spearman’s rho (*ρ*) or Pearson’s *r*, based on the normality assumption. Preliminary analyses will be conducted to identify the frequency, range, variability, and distribution pattern of each variable to apply the most appropriate statistical test when comparisons are needed. Since this RCT has an experimental design with two data collections of the primary, secondary, and tertiary outcomes, the first at baseline (*t*_0_ = 0 weeks) and the second after intervention (*t*_1_ = 24 weeks) in both the intervention and control groups, we will apply a comparative analysis between these measures to establish differences between groups. To evaluate the intervention effect, multilevel mixed-effects regression models with repeated measures will be conducted for each dependent variable. Then, multivariate analyses will be performed, considering the autocorrelation between repeated measures. Both intention-to-treat (ITT) (which measures the effect of assigning an intervention) and per-protocol (PP) analysis (which measures the effect of receiving an intervention) approaches will be applied for the data analysis. All statistical analyses will be conducted using Stata software (Stata, College Station, TX, USA) (version 17.0) for Windows. A *p* value ≤ 0.05 will determine statistical significance.

### 2.6. Variables

The complete set of primary, secondary, and tertiary outcomes will be assessed twice, at the time of enrollment and after the 24-week healthy lifestyle program. The measurements will be performed at school by evaluators previously trained to standardize the measurements and blinded to the group in which participants will be allocated. A summary of all the variables that will be examined in the *Archena Infancia Saludable* project is provided in Table 1.

#### 2.6.1. Primary Outcomes (Schoolchildren)

##### 24-h Movement Behaviors (Accelerometers)

PA and sedentary time will be evaluated by accelerometers. A triaxial accelerometer (Actigraph GT3x, Pensacola, FL, USA) will be used to assess PA, sedentary time, and sleep duration over seven consecutive days. Participants will be instructed to wear the device attached to the nondominant wrist. Since there are nonwaterproof devices, schoolchildren will wear the accelerometers 24 h a day and will only be able to remove them while bathing or swimming. In addition, schoolchildren will have a paper-based diary log to record the time when they go to bed, wake up, and remove the device.

##### 24-h Movement Behaviors (Self-Reported)

Physical activity will be measured using a self-report questionnaire called the Youth Activity Profile—Spain (YAP-S) [46] aimed at assessing physical activity levels and sedentary behaviors in children. The questionnaire was designed to be completed by the children themselves and involves recalling activities from the past seven days. Screen time will be measured in children by asking their parents/guardians about the amount of time the children spend engaged in sedentary screen-based activities as follows: “Approximately, how much time does your child typically spend in front of a screen (on daily average), including computer, tablet, television, videos, video games or cell phone screen?”. The parents or guardians will be asked separately about screen time on weekdays and weekends. Specifically, they will be asked about the average daily amount of time their child spends in front of a screen. To calculate an overall screen time score, the responses to the three questions (two for the weekend and one for weekdays) will be added together after weighting. Sleep duration will be measured by asking parents/guardians about their child’s bedtime and wake-up time separately for weekdays and weekends as follows: “What time does your child usually go to bed?” and “What time does your child usually get up?”. The average daily sleep duration will be computed for each participant by adding together the average nocturnal sleep duration on weekdays (multiplied by 5) and the average nocturnal sleep duration on weekends (multiplied by 2) and then dividing the total by 7. In addition, two additional questions will be asked about *siesta* habits. First, parents/guardians will be asked if their child usually takes a *siesta*, with options of yes or no. Second, parents/guardians will be asked about the duration of the child’s *siesta*, with options ranging from 0–15 min to 120 min or more. A *siesta* is a customary short nap that is usually taken in the early afternoon, typically following the midday meal, and is prevalent in countries with hot weather conditions, such as those found in the Mediterranean area. The school schedule for all schoolchildren is from 09:00 a.m. to 14:00 p.m., which allows time for children to take a *siesta* after this period.

##### Adherence to the Mediterranean Diet

To assess adherence to the MedDiet, the Mediterranean Diet Quality Index for Children and Teenagers (KIDMED) will be used, which has been previously validated in a young Spanish population [14]. The KIDMED ranges from −4 to 12 and is based on a 16-question test. Items reporting unhealthy characteristics related to the MedDiet are scored with −1 point, and those reporting healthy characteristics with +1 point. The sum of all scores from the KIDMED test will be used to categorize into three different levels of adherence: (a) optimal MedDiet (≥ 8 points), (b) improvement needed to adjust intake to Mediterranean patterns (4−7 points), and (c) very low diet quality (≤ 3 points) [14].

#### 2.6.2. Secondary Outcomes (Schoolchildren)

##### Anthropometric Measurements

The weight of the schoolchildren will be assessed using a Tanita BC-545 electronic scale with an accuracy of 0.1 kg, while height will be measured with a Leicester Tanita HR 001 portable height rod with a precision of 0.1 cm. Body mass index (BMI) will be computed by dividing body weight in kilograms by height in squared meters. Additionally, BMI z scores will be determined using the sex- and age-specific thresholds provided by the World Health Organization [47] and the International Obesity Task Force Criteria [48]. The BMI z scores will then be utilized to identify excess weight (i.e., overweight or obesity). Furthermore, waist circumference will be measured to the nearest 0.1 cm at the umbilical level using a measuring tape with a standardized level of tension applied throughout the measurement. The waist-to-height ratio (WHtR) will be calculated, and a WHtR value ≥0.5 will be considered an indicator of abdominal obesity [49].

##### Active Transportation

Active transportation to and from school will be determined by a self-report questionnaire of the PACO (*Pedalea y Anda al Cole*) project [50]. Participants will respond to the following questions: “How do you usually go to school?”, and “How do you usually come back from school?”. Additionally, the second group of inquiries pertains to the method of transportation used for traveling to and from school on a weekly basis. The possible responses include walking, by car, bike, motorbike, bus, or other transport (requesting specific open-ended information in this case).

##### Resting Blood Pressure and Heart Rate

For the purpose of measuring resting blood pressure and heart rate in schoolchildren, an automated blood pressure monitor will be used, which includes a cuff of appropriate size (Omrom^®^ EVOLV HEM-7600T-E, Health-care Co, Kyoto, Japan). The children will be asked to sit in a quiet room with their feet on the ground and back supported for 10 min, after which two readings of their blood pressure will be taken, with the second reading being taken five minutes after the first. The average of the two readings for systolic and diastolic blood pressure will be preserved, and mean arterial pressure will be calculated using the following formula: diastolic blood pressure + [0.333 × (systolic blood pressure—diastolic blood pressure)]. The blood pressure measurements will be categorized using age-, sex-, and height-specific cutoff points provided by the European Society of Hypertension guidelines for children and adolescents [51]. High-normal blood pressure will be defined as systolic or diastolic blood pressure that is equal to or greater than the 90th percentile but less than the 95th percentile for young people aged 0–15 years. Hypertension or percentile hypertension will be defined as systolic or diastolic blood pressure that is equal to or greater than the 95th percentile for young people aged 0–15 years.

##### Sleep-Related Problems

The BEARS (B = Bedtime Issues, E = Excessive Daytime Sleepiness, A = Night Awakenings, R = Regularity and Duration of Sleep, S = Snoring) scale will be used to assess sleep-related issues. The BEARS scale is a screening tool that includes questions related to bedtime problems, excessive daytime sleepiness, night awakenings, regularity and duration of sleep, and snoring. This tool will be used in an interview to screen for the most common sleep-related problems in children and adolescents [52]. The parents/guardians will report the results of the BEARS scale. The Spanish version of the BEARS scale has been found to be valid for screening sleep-related problems in pediatric evaluations [53].

##### Health-Related Quality of Life

Health-related quality of life will be measured by the Child Health Utility 9D (CHU9D) [54,55]. The questionnaire was originally intended for children aged 7–11 years, but it can also be applied for children who are 6 years old with the help of an interviewer [56]. The CHU9D comprises 9 different areas, including worry, sadness, pain, tiredness, annoyance, school-work/homework, sleep, daily routine, and the ability to participate in activities. Each area has 5 different levels indicating increasing severity. The scores from the CHU9D will be utilized in cost-utility analyses [57]. In addition, cost-effectiveness will be assessed by an ad hoc questionnaire answered by parents/guardians, including the number of days in the hospital, pediatrician visits, medicine use and its cost, and study days lost due to health problems during the last 24 weeks.

##### Self-Reported Physical Fitness

The International Fitness Scale (IFIS) will be used to evaluate self-reported physical fitness. This scale comprises five items that use a 5-point Likert scale to ask about the children’s overall perceived physical fitness, as well as their perceived cardiorespiratory fitness, muscular fitness, speed-agility, and flexibility when compared to their peers. The Likert scale includes options for very poor, poor, average, good, and very good physical fitness [58].

##### Academic Performance

At the end of the academic year, the school will provide academic records. Academic performance will be evaluated by two different methods. First, it will be assessed based on the grades obtained in Mathematics, Language, Mathematics and Language combined, and English, as well as the grade point average of these three subjects. These measurements have been used in previous studies as indicators of academic performance [59,60]. Second, academic performance will be evaluated by calculating the average of all the subjects taken by the schoolchildren [61].

